#### Food pantry-level instruments

2.10.3

The Food Pantry Environmental Checklist (FPEC) was developed as part of the FSHP trial (7), and is used to assess the availability of healthy and unhealthy foods and beverages at food pantries. Foods and beverages are categorized based on the United States Department of Agriculture’s five groups: dairy, fruits, vegetables, grains, and proteins. Additionally, there are two more categories for high-sugar and high-fat foods and beverages. Along with food, the FPEC has a section on the food pantries’ policies on procuring, stocking and distributing food items, including questions regarding the number of freezers/refrigerators available and which specific programs donate food, among others (45).

We will use several existing questionnaires in our formative work to develop a pantry-level emergency preparedness questionnaire. We will utilize sections of the Centers for Disease Control and Prevention Crisis Emergency Risk Communications (CERC) Assessment Tool (51), EOC Position Checklists (52), and the Personal Protective Equipment Burn Rate Calculator (53), addressing behaviors in the emergency preparedness training module that will be developed, and based on input from the Baltimore Office of Emergency Management (OEM) to create a scale to assess emergency preparedness among pantries. The instrument will be piloted with a sample of approximately 10 food pantry directors.

#### App feasibility metrics

2.10.4

The SAFPAS app will generate user statistics, including information on level/frequency of user engagement and who is using the app (e.g., clients, food pantry directors/staff, food bank staff). This information will be stored in a database and will be updated daily in a web-based dashboard. We will define user engagement variables and system-generated data to be captured and stored by the system for later analysis, including time(s) and duration of sessions, frequency of use and other technical data (battery charge, connectedness). In addition, select data will be accessible to users in a graphical form through the dashboard.

#### Process evaluation measures

2.10.5

App-generated data will be applied to develop process evaluation measures – including the reach, dose delivered, and fidelity of the SAFPAS intervention implementation (54). The team will develop specific standards for each process evaluation component that will be generated through the SAFPAS app itself. For example, reach would include the number of clients and food pantries using the app; dose delivered would constitute the number of trainings completed by food pantry volunteers; and fidelity would reflect how fully the features of the app are being used. We will monitor our ability to meet set standards, and work to improve as the trial proceeds. Research team members will meet weekly during implementation to discuss progress, address challenges, and adjust delivery.

### Sample size and power

2.11

A sample size calculation was conducted to assess the impact on Aim 3: the change in the healthfulness of client bags (primary outcome). The calculation was based a cluster-level t-test comparing the mean change in FAST scores of client bags at the intervention pantries to those at the comparison pantries. In our calculation, we used the reported mean change in FAST scores in comparison and intervention food pantries from the previous FSHP trial (7) with that hypothesis that there will be a trend toward increased FAST scores among intervention pantry clients compared to clients who are sampled from comparison pantries. Ultimately, sample-size assumed a difference in FAST Scores of 12 points, effect size of 0.8, intraclass correlation of 0.2, type I error of 5%, and power level set at 80%, to lead to a total sample size of 20 stores with 10 per arm and 18 clients per pantry (*n* = 360 at baseline). One pantry was added to each arm of the study to account for possible attrition, leading to the final sample size of 40 pantries. Similarly, we have added 3 clients per pantry to allow for potential drop out and still have necessary power based on our previous trial (7).

For direct comparison of the change in outcome over the intervention period, we will calculate an individual’s change in FAST score over time for each outcome by subtracting the pre-intervention value from the post-intervention value. These changes will then be compared between the intervention groups using cluster-level t-tests or nonparametric Wilcoxon-Mann–Whitney tests, depending on the normality of these individual changes.

The study is not powered to test for differences in secondary outcomes (e.g., nutrition knowledge, BMI, dietary intake, food pantry environment); initial findings will be used as preliminary data for a larger trial.

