### Randomized controlled trial

2.4

For the trial, which will only take place in Baltimore, we will recruit at the food pantry level. We will recruit 10 intervention and 10 control food pantries from a list of member food pantries provided by the Maryland Food Bank, foodpantries.org, listings maintained by colleagues who do work with food pantries, and The Maryland Food System Map list. Only medium and large food pantries will be recruited (>10,000 pounds of food distributed per year) given that small pantries may few staff, volunteers, and clients, and may be open infrequently. Food pantries that have participated in our trials previously will be excluded from participation, as will school- and health-center- based pantries given their potential different distribution systems compared to traditional food pantries. Once a pantry is recruited, we will recruit staff and volunteers (*n* = 100, 5 per pantry), and clients (*n* = 360, 18 per pantry) to be part of the trial using the same inclusion criteria described for formative research. These recruitment numbers are the goal reflect the results of a power and sample size calculation based on showing change in FAST scores.

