### Randomization of food pantries to intervention

2.5

Twenty Baltimore-based food pantries in this group-randomized trial will be first stratified by pantry size, established by the Maryland Food Bank (medium, >10,000 lbs. of food/year; or large, >25,000 lbs. of food/year), with half the pantries randomized to intervention, and half to comparison using a random number generator. Small pantries will be excluded given they may have few staff, volunteers, and clients, and may be open infrequently. By randomizing at the food pantry level, we aim to account for differences such as client population served, food distribution method, infrastructure (e.g., refrigeration), donations from other sources aside from the food bank, and staff/volunteer size.

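### Section 2.11 states a final size of 40 pantries against 20 everywhere else, and does not say whether 10 per arm with 18 clients each already includes the attrition allowance

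*Protocol article*

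**What the plan says.** Section 2.11 of the protocol article bases the size on a "cluster-level t-test comparing the mean change in FAST scores of client bags". The inputs are a 12-point difference, an "effect size of 0.8", an intraclass correlation of 0.2, 5% type I error and 80% power. These are said "to lead to a total sample size of 20 stores with 10 per arm and 18 clients per pantry", with 360 clients at baseline.

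Two attrition additions follow. For pantries: "One pantry was added to each arm of the study to account for possible attrition, leading to the final sample size of 40 pantries". For clients: "we have added 3 clients per pantry to allow for potential drop out".

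The rest of the article keeps to the smaller figures:
- Abstract: 20 pantries and 360 clients.
- Section 2.4: "We will recruit 10 intervention and 10 control food pantries", with 18 clients per pantry (360) and 5 staff or volunteers per pantry (100). It says that these recruitment targets come from the power calculation.
- Section 2.5: "Twenty Baltimore-based food pantries in this group-randomized trial", half to each arm.
- Section 2.9: 10 comparison pantries.
- Section 2.12: app access for 18 selected clients of an intervention pantry.

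**The concern.** The only sentence that names a final sample size contradicts the sentence before it and every other statement of the number of pantries. The pantry is the unit of randomisation and the unit of the cluster-level test, so this is the most important number in the section.

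Behind the wrong figure lies an ambiguity that a one-digit correction would leave in place. Read in order, the calculation gave 10 per arm and 18 clients, and the allowances came afterwards. On that reading the recruitment sections never took up the additions. Alternatively, 10 and 18 already contain the allowances and the calculation gave something smaller, which the article does not state. The reader cannot tell which, and so cannot tell how many pantries and clients must remain at follow-up for the trial to meet its own requirement.

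**Working it through.** **1. The stated figure.** Inputs from section 2.11: 10 per arm, 18 clients per pantry, plus 1 pantry per arm, plus 3 clients per pantry.

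- Pantries: 2 × (10 + 1) = 22. The stated 40 is not reproduced.
- Clients if both additions are made: 22 × (18 + 3) = 22 × 21 = 462. With the pantry addition only: 22 × 18 = 396.
- Forty pantries at 18 clients would mean 40 × 18 = 720 clients, against the 360 stated in the same section.

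**2. The other reading.** If 10 and 18 already include the additions:

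- Base pantries: 2 × (10 − 1) = 18.
- Base clients per pantry: 18 − 3 = 15, so 18 × 15 = 270.
- Adding back: 2 × (9 + 1) = 20 pantries and 20 × (15 + 3) = 360 clients. This matches the recruitment sections exactly.

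**3. Can the stated inputs decide between the readings?** Assumptions: 0.8 is a client-level standardised effect (implied SD 12 / 0.8 = 15 points; no SD is stated), and the 5% level is two-sided (not stated). For k pantries per arm and m clients per pantry, in SD units:

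- variance of a pantry mean: v = (1 + (m − 1) × 0.2) / m
- noncentrality: 0.8 / √(2v / k), with 2(k − 1) degrees of freedom

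At m = 18, v = 4.4 / 18 = 0.2444. At m = 15, v = 3.8 / 15 = 0.2533. Two worked cases:

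- k = 10, m = 18: 0.8 / √(2 × 0.2444 / 10) = 3.62 on 18 df; power 92.8%.
- k = 9, m = 15: 0.8 / √(2 × 0.2533 / 9) = 3.37 on 16 df; power 88.6%.

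| Pantries per arm | Clients per pantry | Power |
|---|---|---|
| 7 | 15 | 77.9% |
| 7 | 18 | 79.3% |
| 8 | 15 | 84.0% |
| 8 | 18 | 85.3% |
| 9 | 15 | 88.6% |
| 10 | 18 | 92.8% |
| 11 | 21 | 95.5% |
| 20 | 18 | 99.9% |

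The smallest number that reaches 80% is 8 per arm, at 15 or at 18 clients. The normal approximation gives about 6 per arm, or about 7 with one cluster added. Neither 9 nor 10 is the minimum, so the inputs do not show which base was used. None of these variants gives 40 pantries.

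**4. What losses would leave.** Suppose 20 pantries and 360 clients are enrolled, and one pantry per arm and three clients per pantry are lost. What remains is 9 per arm with 15 clients, whichever reading is right, and power is 88.6%. The readings differ in whether that remainder is the calculated requirement or falls below it.

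**The case against.** The strongest reply is that the trial's size is not in doubt. The figure 40 appears once. The abstract and the recruitment, randomisation and comparison-group sections all point to 20 pantries, and so do 100 staff at 5 per pantry. Section 2.11 itself says 10 per arm and ties 360 to baseline, which is an enrolment figure. The additions are described in the past tense, and 9 + 1 and 15 + 3 land exactly on 20 and 360, so the allowance may simply be inside the total.

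Most of this stands. A reader might infer from section 2.11 that the size of the trial is undefined, or that it lies anywhere in a two-fold range from 20 to 40 pantries. The documents do not support that, because the operative sections agree on 20 and 360.

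A reader might also infer that power is at risk. On the stated inputs it is not: 9 per arm with 15 clients still exceeds 80%.

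The reply does not remove the wrong figure, and it does not establish that the allowance is inside the total. A base of 9 and 15 is back-calculated and stated nowhere. The section says that the calculation led to 10 and 18.

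**Conclusion.** The point holds as an error in a stated figure together with an unresolved ambiguity. Forty pantries is wrong as written: the section's own arithmetic gives 22, and the rest of the article uses 20. The intended enrolment is very probably 20 pantries and 360 clients. What is left open is whether those numbers stand before the attrition allowance (literal total 22 pantries and 462 clients) or after it (base 18 pantries and 270 clients).

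No power shortfall is shown. Power is about 92.8% with no losses from 20 pantries and 360 clients, and about 88.6% after the full allowed losses. Both figures rest on a client-level effect size of 0.8, an intraclass correlation of 0.2 and a two-sided 5% test. The client-level reading is natural because an intraclass correlation is listed among the inputs. If 0.8 were instead the effect on pantry means, 26 pantries per arm would be needed. That would be a separate question, and it would reproduce neither 20 nor 40.

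**What to change.** In section 2.11, replace 40 pantries with the intended figure, which is 20 if the recruitment sections are right. From the original calculation, state pantries per arm and clients per pantry before the allowance, then the additions, then the enrolled totals, so that the section agrees with the abstract and sections 2.4, 2.5 and 2.9. Do not enter 9 per arm and 15 clients merely because they make the sums work; the sponsor should confirm them first. If the calculation did require 10 per arm and 18 clients, say that the enrolment of 20 and 360 contains no attrition allowance, and give the power after the expected losses.

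If 20 pantries and 360 clients are intended, the cost is a text correction, with no change to recruitment, randomisation or analysis.

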The statistical plan will begin with exploratory analysis to examine broad trends and intervention effects from pretest score/intake to posttest score/intake. We will compare the change in FAST scores between intervention and comparison groups using cluster-level t-tests for normally distributed continuous changes or nonparametric Wilcoxon-Mann–Whitney tests for non-normal continuous changes. Then we will conduct linear mixed-effect models for confirmatory testing of intervention effects, with adjustments. T-tests will be used for normally distributed continuous variables and nonparametric Wilcoxon-Mann–Whitney tests for non-normal continuous variables. We will follow the exploratory analysis with multilevel mixed models. The mixed effects regression models will use change in pantry- and client-level scores over time as outcomes and will be modified to identify intervention effects as well as risk factors in regression analyses. Adjustments for client demographics (age, sex, education, etc.) and pantry-level variables (e.g., pantry size) will be considered. The clients’ “home” pantry will be treated as a random effect. It is possible that our client sample will use multiple food pantries, leading to possible contamination. Thus, we will calculate an overall intervention pantry exposure score and adjust our analyses. However, we anticipate contamination will be mitigated by giving app access to the 18 selected intervention pantry clients only. Posttest scores will be response variables in the models. The primary hypothesis is: compared with comparison pantries, client bags in intervention pantries will have a greater improvement (larger positive change) in FAST scores from pre-intervention to post-intervention. We will compare the mean change in FAST scores of participant bags from the intervention pantries to those from the comparison pantries. We expect that the SAFPAS intervention will result in a mean improvement (positive mean change) in FAST scores that is 12 FAST points better than the mean change in the comparison group.

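### The Wilcoxon fallback for the FAST comparison is chosen on client-level normality and has no stated cluster level; run on client changes its false-positive rate would be about 31–35%

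*Protocol article*

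**What the plan says.** Section 2.5 randomises 20 pantries, half to each arm, stratified by pantry size. Section 2.11 sizes the trial on a cluster-level t-test of mean change in FAST, with "intraclass correlation of 0.2" and "20 stores with 10 per arm and 18 clients per pantry".

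Section 2.11 then sets out a direct comparison. Each client's change is the post-intervention value minus the pre-intervention value, and these changes are compared between arms "using cluster-level t-tests or nonparametric Wilcoxon-Mann–Whitney tests, depending on the normality of these individual changes". The step carries no exploratory label there.

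Section 2.12 gives the rule again for FAST: "cluster-level t-tests for normally distributed continuous changes or nonparametric Wilcoxon-Mann–Whitney tests for non-normal continuous changes". A later sentence has no cluster level for either test: "T-tests will be used for normally distributed continuous variables and nonparametric Wilcoxon-Mann–Whitney tests for non-normal continuous variables".

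Section 2.12 places this step inside an opening exploratory analysis. It names linear mixed-effect models for confirmatory testing, with the client's home pantry as a random effect.

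**The concern.** There are two faults in the rule as written.

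- **The criterion is wrong.** A cluster-level t-test works on one summary per pantry, about 20 values. Its normality assumption concerns those summaries, not the 270 to 360 client changes. Client changes can be clearly non-normal while means of 15 to 18 of them are close to normal.
- **The alternative test has no stated unit.** In 2.12 the cluster label belongs to the t-test phrase, and the Wilcoxon test has its own phrase without it. The values that 2.11 names for comparison are individual changes. Read literally, failing the normality check moves the analysis from 20 pantry means to some 300 client values treated as independent.

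At stake is the validity of the p-value from the comparison that 2.11 puts forward for the primary outcome. The unlabelled sentence in 2.12 carries the same risk to any other client or staff outcome tested that way.

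**Working it through.** **Inputs from section 2.11**

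- Difference and effect size: "sample-size assumed a difference in FAST Scores of 12 points, effect size of 0.8". The implied SD of change is 12 / 0.8 = 15.
- Intraclass correlation 0.2, taken here to apply to the change in FAST, the quantity on which the trial is sized.
- "type I error of 5%, and power level set at 80" per cent. Sidedness is not stated; two-sided is assumed.
- Ten pantries per arm and 18 clients each. The attrition allowances are one pantry per arm ("One pantry was added to each arm of the study to account for possible attrition") and three clients per pantry, so the lower case is 9 pantries per arm and 15 clients each.

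**1. The plan's own sample size**

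- Unclustered n per arm = 2 × (1.96 + 0.84)² × 15² / 12² ≈ 24.5, rounded up to 25.
- Design effect = 1 + (m − 1) × 0.2, which is 3.8 at m = 15 and 4.4 at m = 18.
- Pantries per arm = 25 × 3.8 / 15 = 6.3, or 25 × 4.4 / 18 = 6.1. With one extra cluster per arm this is 7.1 to 7.3; exact t power needs 8.
- Power of the cluster-level t-test is 88.6% at 9 × 15 and 92.8% at 10 × 18.

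The stated size is not reproduced; it is larger than its inputs require, on the safe side. That does not bear on this point, but these are the inputs used below.

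**2. False-positive rate of a client-level test**

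A test that treats clients as independent understates the variance of the arm difference by the design effect (DE). Its true size is approximately 2 × [1 − Φ(1.96 / √DE)].

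| Clients per pantry | DE | 1.96 / √DE | Size |
|---|---|---|---|
| 15 | 3.8 | 1.005 | 31.5% |
| 18 | 4.4 | 0.934 | 35.0% |

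This is 6.3 to 7.0 times the nominal 5%. At lower intraclass correlations (15 to 18 clients) the formula gives 13.3–15.0% at 0.05 and 20.6–23.3% at 0.10.

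**3. Simulation under no effect**

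The formula is for a comparison of means, so the rank test was simulated: 2,000 runs per setting; intraclass correlation 0.2; 9 × 15, 10 × 15 and 10 × 18 per arm; normal pantry effects; client deviations normal, exponential, or t with 3 df.

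| Test | Normal | Skewed or heavy-tailed |
|---|---|---|
| Wilcoxon on client changes | 32–33% | 38–43% |
| Wilcoxon on pantry means | 3.8–4.8% | 3.6–4.6% |
| Cluster-level t-test | 4.4–6.3% | 4.1–5.7% |

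The cluster-level t-test stays near 5% even when client changes are clearly non-normal, so non-normality of client changes gives no reason to leave it.

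**4. The switching rule as a whole**

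The protocol names no normality test. Assuming Shapiro-Wilk at 5% in either arm, then Wilcoxon on client changes, the overall size was 7–9% with normal data (about 10% of runs switched) and 38–42% with the non-normal shapes. These figures illustrate; they depend on the assumed test and distributions.

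**The case against.** **The step is labelled exploratory.** Section 2.12 puts the t-test/Wilcoxon comparison in an exploratory stage and makes a mixed model with a pantry random effect confirmatory. A reader might infer that the trial's deciding test has a 31–35% error rate. The documents do not support that: on the text of 2.12, the confirmatory model accounts for clustering. This part of the objection stands. It does not remove the point, because 2.11 offers the t-test/Wilcoxon step as the direct comparison without that label, and the power calculation rests on its t-test.

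**The word cluster-level may cover both tests.** In 2.11 alone that reading is possible, and the authors plainly know that pantries are the unit. On pantry means there is no inflation. But 2.12 splits the two tests into separate phrases, then drops the label from both, and both sections speak of individual or continuous changes. The client-level reading is the more natural one, though not certain.

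**Non-normality is not shown.** FAST runs from 0 to 100, but the analysed quantity is a change and the document gives no distribution for it. How often the switch would be triggered is unknown. This also stands.

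**Staff outcomes.** No staff intraclass correlation is given, so no error rate is claimed for them. The study is not powered for secondary outcomes, but that does not make an unclustered test valid.

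**An analysis plan not shown may settle the unit.** It may. The point here is the criterion and the wording that the article itself states.

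**Conclusion.** The point holds in limited form; it should be fixed. Choosing the test by normality of client changes is wrong on either reading of the text, because the t-test's units are pantry means. The size of the error is conditional: if the Wilcoxon test is run on client changes, its false-positive rate is about 31% to 35% by formula, and was 38–43% in simulation with clearly non-normal changes. If it is run on pantry means, it is about 5% or below. The 31–35% rests on the protocol's intraclass correlation of 0.2, 15 to 18 clients per pantry, and a two-sided 5% level. It applies to the step in 2.11, not to the confirmatory mixed model in 2.12. The two sections do not agree plainly on which of these decides the primary outcome.

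**What to change.** 1. In 2.11 and 2.12, delete the choice of test based on normality of individual changes.
2. State that every t-test or Wilcoxon comparison between arms, for client or staff outcomes, uses one summary value per pantry. Replace the unlabelled sentence in 2.12 accordingly.
3. If a distribution-free check is wanted, a permutation test that reallocates pantries within the two size strata would serve. This is optional.
4. State in both sections that the mixed model with a pantry random effect is the single deciding test for the primary outcome, and that the pantry-level comparison is supportive.

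The cost is wording in the protocol and analysis plan. No new data, recruitment or follow-up is needed.
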